### Outcomes

The primary outcome of this trial will be the change in systolic blood pressure. It will be measured before, on each month interval and after completion of the intervention (at 90 days) at outpatient clinical settings with an aneroid sphygmomanometer (BP set). The secondary outcome will be the body mass index (BMI) and heart rate (HR). Both will be assessed at baseline and after the intervention.

### Sample size

Sample size calculations are based on continuous outcome superiority trial; assuming 7 mmHg of mean difference in systolic blood pressure between control and experimental groups [14]. This study requires 140 participants to have a 80% chance of detecting the proposed change in systolic blood pressure in the experimental group as significant at the 5% level, after adjusting 20% dropout rate [22]. A standard deviation of outcome variable was estimated as 13 mmHg in both arms [23]. As recommended by the literature, design effect of this multicenter study is considered very negligible and excluded from the calculation [24].

### Recruitments

Both the DAHC research staff and clinicians will be trained on the protocols and procedures of the study. They will screen the hypertensive patients attending DAHCs for the eligibility criteria; obtain written consent; enroll the eligible participants for the study; and send the participants’ name for centrally generated stratified blocks for randomization (Fig. 2). That is to allocate the participants in treatment and control arm. The randomization scheme will consist of a sequence of blocks such that each block will contain a pre-specified number of treatment assignments in random order. For this, out of total 20 subjects in each center, 4 blocks of various sizes will be randomly created and participants will be allocated in two-arms achieving balance across groups (10 in treatment; 10 in control). Participant list will be prepared by someone not involved in the recruitment to the trial and will be shared each center.

**Fig. 2 Fig2:**
[figure not shown]
Flow chart of phases of study. Total 140 study participants from seven study sites (20 per site) will be enrolled in the study. Both arms (treatment and control) will contain equal numbers of participants (10 in each arm) at each center (through stratified block randomization)

### Data collection

Baseline and post-intervention data on primary and secondary outcomes will be collected during a face to face interview. Additionally, anthropometric measurements and clinical examination data will also be collected. This study will also collect pre-intervention information on tobacco use, alcohol consumption, dietary patterns and physical activity.

#### Face-to-face interview

The interview questionnaire will cover participant’s demographics and health behavior. The health behavior questions are designed to assess tobacco use, alcohol consumption, fruit and vegetable consumption and physical activity. Tobacco, alcohol and diet related questions will obtain information on frequency and pattern of use or intake. These questions are particularly adopted from STEPs survey questionnaire tool [25]. For measuring physical activity level, seven days history of physical activity will be recorded and converted into Metabolic Equivalent of Task (MET) value using available guidelines [26].

#### Anthropometric measurement

To assess the change in BMI, height and weight will be measured using portable stadiometer and digital scales [27].

#### Clinical measurement

Blood pressure will be measured with an aneroid sphygmomanometer (BP set) in outpatient settings. Before taking the measurements, participants will be requested to rest for 15 min with legs uncrossed. Three readings of the systolic and diastolic blood pressure will be recorded in each five-minute interval. The average of second and third readings will be used for analysis.

### Data management and analysis

Data will be complied, edited, processed and analyzed using Epidata 3.1 and Stata 14.0. Analyses will be performed based on the intention-to-treat (ITT) principle. In the case of missing data and lost to follow-up, the last data obtained from a participant will be used for analysis. Similarly, for the participants who will start new medication or change the dose of existing medication during the study period, data will be replaced via the last observation carried forward method. Sensitivity analyses will be performed to test whether the findings from the available-case analysis are consistent and will lead to similar conclusions as in the primary analysis. A per-protocol (PP) analysis will also be carried out for only those patients who will complete the treatment as allocated.

Baseline characteristics will be presented in tables with frequency, proportions and mean ± standard deviation; frequency comparisons will be made using Chi-squared tests, and independent sample t-tests for mean differences. Primary and secondary outcomes will be analyzed with mixed-effects linear regression models where each health center will allow to have a random intercept. Potential confounding variables including smoking, alcohol consumption and physical activity will be treated as fixed factors. Both models will include baseline assessments as covariates. All tests will be two-tailed and *p* < 0.05 will be considered statistically significant.

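### Carrying the last observation forward in the primary analysis biases the day-90 blood-pressure estimate, by an amount and in a direction set by when and in which arm participants drop out

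*Protocol article*

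**What the plan says.** All references are to the protocol article.

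- **Missing data (Data management and analysis).** "In the case of missing data and lost to follow-up, the last data obtained from a participant will be used for analysis". The governing principle is stated as "Analyses will be performed based on the intention-to-treat (ITT) principle".
- **Sensitivity analysis (same section).** "Sensitivity analyses will be performed to test whether the findings from the available-case analysis are consistent and will lead to similar conclusions" as the primary analysis. LOCF is therefore the primary rule, and the observed-data analysis is the check on it.
- **Model (same section).** The outcomes go into "mixed-effects linear regression models where each health center will allow to have a random intercept", with baseline as a covariate. The centre intercept is the only random term named.
- **Timing (Outcomes).** Systolic pressure: "It will be measured before, on each month interval and after completion of the intervention (at 90 days". For BMI and heart rate: "Both will be assessed at baseline and after the intervention".
- **Follow-up visits (Intervention).** Visits are every 30 days, with blood pressure and BMI taken at each. The sentence follows one about the treatment group.
- **Dropout (Sample size).** The 140 participants are the number needed "after adjusting 20% dropout rate".

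The same device is applied to participants whose medication changes ("data will be replaced via the last observation carried forward method"). That raises separate questions and is not sized here.

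**The concern.** LOCF treats a participant's pressure as frozen from the last visit attended. The trial's own premise is that it is not frozen. Both arms receive lifestyle education, which the Background credits with lowering systolic pressure by 4 to 9 mmHg. Entry requires a raised reading, so some regression to the mean is likely. Yoga is expected to add 7 mmHg by day 90. A carried value, which may be the baseline itself, therefore tends to miss part of the fall.

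If dropout is equal, the treatment effect is diluted. If it is unequal, part of the common fall is counted as a difference between arms. Unequal dropout is plausible: the trial is unblinded, and only the yoga arm has five two-hour training days and 90 days of home practice. About 28 of 140 primary values (20%) could be carried forward.

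**Working it through.** **Inputs from the document.** Difference 7 mmHg, SD 13 mmHg, 80% power, 20% dropout, N = 140 (Sample size); two-sided 5% (Sample size; Data management and analysis); 70 per arm (Recruitments: 10 + 10 in each of seven centres).

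**Assumptions, none given by the document.** Yoga effect of 3, 5 and 7 mmHg at 30, 60 and 90 days; a linear fall common to both arms; the dropout split; dropout independent of outcome; the carried visit equally likely to be baseline, day 30 or day 60 unless stated.

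**1. The plan's own figure.** A two-sample t-test for 7/13 needs 56 per arm; 56/0.8 = 70 per arm, 140 in total. This reproduces N. Power with 56 observed per arm is 80.6%, so N assumes that dropouts contribute nothing.

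**2. Equal 20% dropout.** Expected estimate = 0.8 × 7 + 0.2 × E, where E is the effect reached at the carried visit. Power is for an unadjusted t-test with 70 per arm counted.

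| Carried visit | E | Estimate (mmHg) | Power |
|---|---|---|---|
| Always baseline | 0 | 5.60 | 71.6% |
| Spread equally | (0+3+5)/3 = 2.67 | 6.13 | 79.1% |
| Always day 30 | 3 | 6.20 | 80.0% |
| Full effect already reached | 7 | 7.00 | 88.6% |

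**3. Unequal dropout, true effect 7, common fall 5.** The yoga fall is 12 at day 90; its mean carried fall is (0 + 4.67 + 8.33)/3 = 4.33. Control: 5 at day 90; mean carried fall (0 + 1.67 + 3.33)/3 = 1.67.

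- Yoga loses 30%, control 10%: (0.7 × 12 + 0.3 × 4.33) − (0.9 × 5 + 0.1 × 1.67) = 9.70 − 4.67 = 5.03 mmHg.
- Reversed: (0.9 × 12 + 0.1 × 4.33) − (0.7 × 5 + 0.3 × 1.67) = 11.23 − 4.00 = 7.23 mmHg.

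**4. No true effect, 30%/10% split.** A carried value misses on average two thirds of the common fall c, so the false difference is (0.30 − 0.10) × (2/3) × c. This is 0.93 mmHg for c = 7 and 1.33 mmHg for c = 10. It goes against yoga if yoga loses more, and in its favour if control does. The value 7 lies inside the Background's 4 to 9 mmHg range; 10 lies just above it.

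**5. Simulation.** 10,000 runs per case, 70 per arm, SD 13, correlation between visits 0.5 or 0.6, baseline-adjusted, centre left out.

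- Type I error of LOCF, 30%/10% split: 7.5 to 8.6% for c = 7 and 10.9 to 11.3% for c = 10. Observed cases: 4.7 to 5.6%.
- Direction, for c = 7 with yoga losing more: 7.0 to 7.6% of runs reject against yoga and 0.5 to 0.7% in its favour.
- Equal dropout, no effect: bias about zero and type I error about 5%.
- Standard error: the mean model value and the empirical SD of the LOCF estimate agree within 0.03 mmHg (for example 1.91 against 1.92).

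**6. Secondary outcomes.** The Outcomes section gives heart rate two measurements only, so a dropout's carried value is the baseline and the change is exactly zero. For BMI, Outcomes implies the same, but Intervention lists BMI at every follow-up visit. The two sections conflict.

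**The case against.** The strongest reply is that the plan contains its own check. The observed-data comparison would show whether carried values drive the result, and the model adjusts for baseline. That stands as mitigation. But the headline estimate remains LOCF, and the article does not say what follows if the two analyses disagree.

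Four stronger readings are tempting and are not supported.

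- **That power falls to 72%.** Under equal dropout this needs every dropout to leave before day 30. With dropout spread over visits, power stays at about 79 to 80%, close to plan.
- **That the confidence interval is falsely precise because imputed values count as real.** In simulation the LOCF standard error matches the actual variability of the estimate.
- **That LOCF inflates false claims of benefit.** If the more burdened yoga arm loses more, the error runs against yoga. The error in its favour needs control to lose more. Equally, LOCF cannot be defended as reliably conservative.
- **That every BMI dropout has zero change.** The Intervention section points to interim BMI values, so this is firm only for heart rate.

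It is also fair to say that the 30%/10% split and the common fall are assumed, and that dilution vanishes if the full effect is already present at the last visit seen.

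**Conclusion.** The concern holds as one of bias in the primary estimate. Under equal 20% dropout the loss is about 0.8 to 0.9 mmHg of the planned 7 when participants leave at different visits, and 1.4 mmHg at worst. Under the assumed 30%/10% split with a 5 mmHg common fall, the same true effect is reported as about 5.0 or 7.2 mmHg, depending on which arm loses more. With no effect and a 7 to 10 mmHg common fall, type I error is roughly 7 to 11%.

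The sizes rest on the assumed time course, common fall and split; the mechanism needs only that pressure changes during follow-up. Observed cases stay unbiased in these runs because dropout was made independent of outcome, which real dropout may not be. Given the planned check and the moderate size of the bias, this should be fixed; it does not by itself invalidate the trial.

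**What to change.** - **Primary systolic analysis.** Replace LOCF with a likelihood-based repeated-measures mixed model of baseline, 30-, 60- and 90-day systolic pressure, with treatment-by-visit terms, participant-level covariance and centre. Make the day-90 contrast primary.
- **Interim visits.** State that monthly systolic pressure is taken in both arms; the Intervention section leaves this open for controls. If controls have no interim visits, use a baseline-adjusted day-90 model on observed data, or multiple imputation, instead.
- **Heart rate and BMI.** Use a baseline-adjusted likelihood or multiple-imputation analysis for heart rate. Reconcile Outcomes with Intervention on when BMI is measured, and treat BMI as heart rate if it is measured only twice.
- **LOCF.** Keep it, if wanted, as a sensitivity analysis.

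**Cost.** A change of analysis wording only, with no change to N: 56 observed per arm already gives 80.6% power. No new data are needed if monthly pressure is taken in both arms. The interval will be somewhat wider than under LOCF. In the simulation with equal dropout, the observed-data standard error was 11 to 12% larger (2.13 against 1.91, and 1.97 against 1.77). The replacement assumes data missing at random, which is weaker than a frozen pressure but still an assumption.

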### Data and safety monitoring

To ensure the data safety, a data monitoring and quality assurance team will review the procedures for maintaining the confidentiality of data, and the quality of data collection, management and analyses. They will assess the missing information and errors in the dataset. They will also closely monitor recruitment, participation status, treatment compliance, regular follow-up and overall quality of research, and provide necessary feedback to the study team.

The central and district research team will review participants’ data regularly to ensure safety of the trial. Research Investigators, mostly DAHC clinicians, located in each district will be responsible for reporting serious adverse events and unanticipated problems to the Principal Investigator, who will inform Ethical Review Board (ERB) within 48 h of the events. The district research team will also quickly follow up, assess and treat or refer the participants as required.

## Discussion

Hypertension is emerging as one of the major public health concerns in Nepal. Risk factors survey of the non-communicable disease (NCD) reported that 25.7% of all study population had hypertension [28]. Similarly, large proportions of hypertensive participants often have uncontrolled blood pressure [29].

Global action plan for the prevention and control of non-communicable diseases envisages for a 25% relative reduction in the prevalence of raised blood pressure in the next 10 years. Nepal has a well formed contextualized plan [30]. Interestingly, yoga as a health promotion measure has been recently established via the Urban Health Promotion Centers. Similarly, Department of Ayurveda introduced five days of yoga training to its sub-centers’ staffs for integrating yoga in prevention and control of NCDs. However, we still do not have sufficient evidence on the effect of yoga on hypertension prevention and control in Nepalese community. Therefore, this study expects to generate evidence that will be widely applicable for assisting blood pressure control and well-being in clinical and community settings in Nepal. It will be conducted in existing primary healthcare settings where the intervention package will be delivered by the government staffs at their respective OPDs. Such real-life routine practice settings for intervention would possibly increase the likelihood of generability and applicability of the study findings [31]. If proven effective, yoga can be integrated with medication as an adjunctive therapy for blood pressure control in similar low resource settings of Nepal and developing countries.

This study is not designed to determine which components of the yoga intervention will have an effect on blood pressure. To minimize errors in blood pressure measurement, data enumerators (medical persons) will be uniformly trained in blood pressure measurement including proper timing and positioning of the cuff and the patient.

## Abbreviations

BMI: Body Mass Index
BP: Blood Pressure
CAM: Complementary and alternative medicine
CTRI: Clinical Trial Registry- India
CVD: Cardiovascular Disease
DAHC: District Ayurveda Health Center
DBP: Diastolic Blood Pressure
DoA: Department of Ayurveda
ERB: Ethical Review Board
HR: Heart rate
ITT: Intention to treat
MET: Metabolic Equivalent
NCD: Non-communicable disease
NHEICC: National Health Education Information and Communication Center
OPD: Outpatient department
PP: Per protocol
SBP: Systolic Blood Pressure
ToT: Training of Trainers
